#### End of Research Visit

The last visit made on D28 for patients for patients who survived to this date, will be identical to previous visits.

### Statistical Analysis

#### Descriptive Analysis

A descriptive analysis of inclusions and monitoring of the protocol will be carried out. The main analysis will be carried out according to the intention to treat principle. Only patients who have withdrawn their consent can be excluded from the analysis. Patients who have decided to discontinue the management planned for the trial, lost to follow-up, or discontinued the trial will be included in the analysis. In general, the quantitative variables will be described by their median and their first and their third quartiles and the qualitative variables will be described by the frequencies of the modalities and the associated percentages. The epidemiological and clinical characteristics of the patients at inclusion will be described by group, without statistical tests being carried out. The protocol violations, the causes of abandonment and loss of sight and the characteristics of these patients will be detailed.

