#### Inclusion Criteria

- Adult patient, hospitalized in intensive care for COVID-19, having required mechanical ventilation for at least 24 h.- Not sedated or having a good awakening (Richmond Agitation Score- Sedation Scale (RASS)> −3 at the time of inclusion (42) within 48 h of stopping sedation.- Able to answer yes or no to simple questions.- Having significant dyspnea (level≥ 4) on the A1 scale of the Multidimensional Profile of Dyspnea (MPD-A1≥ 4) (1, 41).- Signature of informed consent by the patient or his family member.

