### Evaluation Criteria

#### Primary Endpoint

- Measurement of the differential of the score on the A1 subscale of the Multidimensional Dyspnea Profile (MPD-A1) (from 0 to 10): between before and after the use of tDCS. This primary judgment criterion will be assessed by an independent, blind observer. The differential will be measured between 30 min before the procedure and 30 min after.

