#### Selection and Inclusion Visit

Inclusion will be made when all the inclusion and non-inclusion criteria are verified and the patient has given informed consent to participate in the study. During inclusion and before the start of the single session of the protocol, the following clinical, drug, and other co- variable data will be collected. These data are in principle systematically measured in intensive care patients.

Demographic data (age and sex), the reason for admission; medical history (neurological, respiratory, cardiological) initial severity by the SAPS-II score (57), the number of organ failures by the SOFA score (58), neurological assessment scores (Glasgow, FOUR score) (59); CAM-ICU (44) and the RASS score (to assess depth of sedation (42). The determinants of secondary cerebral aggression of systemic origin: body temperature, blood pressure, PaO2, PaCO2, natremia, glycemia. The neurological examination which includes: examination of the cranial pairs (spontaneous eye movements, pupil size, photo-motor reflex, oculo-cephalogyr reflex, corneal reflex, reaction to Pierre Marie-Foix's maneuver, cough reflex), the search for archaic reflexes (corneo- mandibular, palmo- mental, yawning, chewing, grasping), osteo-tendinous, and plantar skin reflexes.

The practical implementation of the protocol will consist of a single session of ~1 h 30 m and will include the three stages described in Figure 1. After inclusion and randomization, the set of parameters studied will be measured for each patient, for 30 min before using tDCS, then for 30 min after stopping tDCS. The tDCS will be applied for 30 min to the cortical representation area of the primary motor area and the supplementary left motor area.

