#### Calculation Hypotheses for the Number of Subjects Required and Result

The MDP-A1 subscale of the Multidimensional Dyspnea Profile is the main evaluation criterion of this study. This subscale is similar to the visual analog scale. Assuming a difference of 1 (on the primary efficacy endpoint, superiority study) between one of the 2 experimental groups and the placebo group and a standard deviation of 1, with a first species risk (alpha risk) of 2.5% (to take into account the 2 comparisons of each experimental group with placebo) and a power of 80% (beta risk at 20%), it will be necessary to include 21 patients per group or 63 patients in total. This number is consistent with that of other studies in tDCS (29, 60, 61).

The main analysis will be carried out according to the intention to treat principle. Only patients who have withdrawn their consent can be excluded from the analysis. If the period of inclusion in the research is still active, patients who have withdrawn their consent will be replaced. Patients who have decided to discontinue treatment planned in the trial, lost to follow-up or discontinued from the trial will be replaced, as will patients for whom there have been technical problems. Analyzes will be carried out with the intention of treating. Regarding missing data issue, in case of patient drop-out, in order to clearly understanding of the effectiveness of the therapy, we will first report results based on the completed cases, then secondarily with mixed-model or similar approaches which take into account partially available data, and finally with multiple imputation techniques.

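### Patients who withdraw consent may be excluded and replaced at any time up to Day 28, even when their primary MPD-A1 change is already recorded

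*Protocol article*

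**What the plan says.** Under Descriptive Analysis the protocol article states "The main analysis will be carried out according to the intention to treat principle", and then "Only patients who have withdrawn their consent can be excluded from the analysis". Both sentences recur in the sample-size section (Calculation Hypotheses for the Number of Subjects Required and Result), which adds "If the period of inclusion in the research is still active, patients who have withdrawn their consent will be replaced". Neither section says when the withdrawal must occur for exclusion to apply, or what happens to ratings already taken.

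Descriptive Analysis treats other departures differently: "Patients who have decided to discontinue the management planned for the trial, lost to follow-up, or discontinued the trial will be included in the analysis".

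The timing of the endpoint is explicit under Primary Endpoint: "The differential will be measured between 30 min before the procedure and 30 min after". Selection and Inclusion Visit describes one session of about 1 h 30 min. Research Calendar sets each patient's participation at 28 days.

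**The concern.** For almost all of the 28 days the primary outcome has already been measured. A patient who withdraws consent on Day 5, for example, has both MPD-A1 ratings and leaves no gap in the primary data. The rule nevertheless lets that patient's result be taken out of the randomised comparison and a new patient be entered instead.

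Withdrawal after the session can depend on how the session went, for instance on absence of relief or on discomfort. If so, the rule removes selected results from a randomised arm. Any bias could go in either direction, and it would fall on the primary contrast. The missing-data steps in the sample-size section (completed cases, then mixed models, then multiple imputation) concern drop-out with partial data. They do not bring back a patient who has been placed outside the analysis.

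**Working it through.** **1. Timing.** The session has three stages of 30 min each (before, during and after tDCS), so 3 × 30 = 90 min. The MPD-A1 change is fixed by the end of it. Exclusion for withdrawn consent has no time limit, so it can apply from then until Day 28.

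**2. The plan's own sample size.** Inputs from the sample-size section are a difference of 1, SD 1, alpha 2.5% per comparison and power 80%. Sidedness is not stated; two-sided is assumed because it reproduces the figure.

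- Normal approximation: n = 2(z₀.₉₈₇₅ + z₀.₈₀)² × SD²/difference² = 2 × (2.241 + 0.842)² = 19.01, so 20 per group.
- Exact t calculation: 20 per group gives 79.3% power and 21 gives 81.5%. The stated 21 per group (63 in total) is reproduced and is not in dispute.
- If both compared groups shrank without replacement, power would be 79.3% at 20, 76.8% at 19 and 74.1% at 18 per group.

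**3. Worst-case shift in the difference.** Assumptions: 21 per arm, SD 1, no true effect, and the k patients with the least improvement leave one active arm only. The expected values of the three lowest of 21 standard normal observations are −1.889, −1.434 and −1.160, with cumulative sums of 1.889, 3.323 and 4.483 in size. Without replacement the mean of that arm rises by sum/(21 − k). With k fresh replacements it rises by sum/21.

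| k | Without replacement | With replacement |
|---|---|---|
| 1 | 1.889/20 = 0.09 | 1.889/21 = 0.09 |
| 2 | 3.323/19 = 0.175 (0.18 in simulation) | 3.323/21 = 0.16 |
| 3 | 4.483/18 = 0.25 | 4.483/21 = 0.21 |

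The plan's assumed effect is 1 point, so these shifts are also the fraction of that effect: up to about a quarter.

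**4. Worst-case false claims favouring tDCS.** These come from simulation of t-tests at two-sided 0.025, so the nominal rate in that direction is 0.025/2 = 1.25%. Repeat runs differ by about 0.1 to 0.2 percentage points.

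| k | Without replacement | With replacement |
|---|---|---|
| 0 | 1.25% | 1.25% |
| 1 | 2.9% | 2.9% |
| 2 | 5.4% | 4.9% |
| 3 | 8.5% | 7.2% |

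Replacement reduces the distortion only slightly, because fresh patients do not restore the poor results that were removed.

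**5. Milder scenarios (with replacement).**

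- Withdrawal unrelated to outcome: no bias, and the two-sided error stays near 2.5%.
- The k poorest responders leave both compared arms equally: no bias in the difference. The two-sided error is still about 3.7%, 4.1% and 4.6% for k = 1, 2, 3, because trimming the tails makes the arms look less variable than they are.

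**The case against.** The strongest reply is that this is a narrow exception, declared in advance and in common use. It may reflect consent or data-protection duties. Exclusion is worded as a possibility, replacement depends on inclusion still being open, and a withdrawal may come before any post-session rating exists. Patients who merely stop taking part are kept by the next sentence of Descriptive Analysis, so only formal withdrawal of consent is affected. The patient and the observer of the primary endpoint are blinded. All of this stands, and it limits the point to what the text permits. It does not remove it. The exclusion is stated in two sections with no condition on timing, so it is a fixed rule and not a detail left to a document that is not shown. Blinding to arm does not stop withdrawal from depending on felt relief.

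Three stronger readings are tempting, and the documents do not support them.

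- *Known results will be removed.* The text allows this but does not require it, and nothing suggests that anyone would select on the result.
- *Late withdrawals are to be expected because relatives may sign.* Inclusion Criteria accepts "Signature of informed consent by the patient or his family member", while Selection and Inclusion Visit says "the patient has given informed consent to participate in the study". Later refusal by a patient entered on a relative's signature is possible. However, patients must be able to answer simple questions and refusal is an exclusion criterion, so they can object before the session. No withdrawal rate is given. The difference in consent wording is a side issue.
- *Replacement hides the loss.* Descriptive Analysis promises a description of inclusions and details of violations and causes of abandonment, although it does not name consent withdrawals.

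It is also fair to say that the fix below does not close the gap completely: an explicit objection to data use would still remove a known result.

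Separately, the sample-size section says that patients "lost to follow-up or discontinued from the trial will be replaced, as will patients for whom there have been technical problems", which sits awkwardly with keeping discontinued and lost patients in the analysis. That needs its own reconciliation. The present point would remain after it.

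**Conclusion.** The point holds as a statement of what the plan allows: a recorded primary result can be taken out of the intention-to-treat comparison, and the patient replaced while inclusion is open, solely because consent was withdrawn later. It is not a finding that this will happen or that the trial will be biased.

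The figures in the working are upper bounds for one to three withdrawals. They rest on SD 1, no true effect, and loss of exactly the poorest responders from a single active arm. They do not forecast what will happen. The change is worth making because in an arm of 21 even one selected loss more than doubles the false-claim rate in the worst case (1.25% to about 2.9%), and the remedy is inexpensive. The sample size itself is sound.

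**What to change.** In both Descriptive Analysis and the sample-size section, replace the exclusion and replacement sentences on consent withdrawal with wording to this effect:

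- Withdrawal of consent ends further data collection.
- Data collected up to withdrawal, including the Day 0 MPD-A1 ratings, are analysed in the randomised arm unless the patient explicitly objects to their use.
- A patient with both ratings whose data remain usable is not replaced.
- Withdrawals and objections are reported by arm, with their timing.

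The consent and withdrawal form should offer the two choices separately: stop further collection, or also refuse use of data already held.

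The cost is a protocol and consent-form amendment. No extra patients or procedures are needed, and power stays at 81.5% with 21 usable patients per arm. Explicit objections would still remove some data, but they would be visible by arm and timing.

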#### Primary Judgment Criterion

The studied parameters will be measured during the 30 min before (pre) and 30 min following (post) the use of tDCS in all three conditions (tDCS anodal, tDCS cathodal, and tDCS placebo). The placebo tDCS condition is the control condition (fictitious stimulation). The different measures of the judgment criteria will be carried out by one of the investigating doctors blinded in the randomization arm. In order to test the effect of tDCS, the judgment criteria will be compared according to the different experimental conditions (anodal tDCS, vs. cathodal, vs. placebo tDCS). Each experimental arm will be compared to the placebo group at risk 0.025 using Students *t*-test and applying Bonferroni correction if needed.

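### The primary t-test on the MDP-A1 change is valid and matches the sample size, but one three-arm model adjusted for baseline would give equal or better precision from data already collected

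*Protocol article*

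**What the plan says.** All references are to the protocol article.

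- **Endpoint** (Primary Endpoint): "Measurement of the differential of the score on the A1 subscale of the Multidimensional Dyspnea Profile", on a 0 to 10 scale. On timing: "The differential will be measured between 30 min before the procedure and 30 min after".
- **Test** (Primary Judgment Criterion): "Each experimental arm will be compared to the placebo group at risk 0.025 using Students" t-test. The section names no covariate and no joint model of the three arms.
- **Entry** (Inclusion Criteria): "Having significant dyspnea (level≥ 4) on the A1 scale of the Multidimensional Profile of Dyspnea".
- **Sample size** (Calculation Hypotheses for the Number of Subjects Required and Result): difference 1, standard deviation 1, 80% power, "with a first species risk (alpha risk) of 2.5% (to take into account the 2 comparisons of each experimental group with placebo". The result is 21 per group, 63 in total.
- **Other models** (same section): mixed models appear only as a second step for missing data.
- **Secondary criteria** (Secondary Judgment Criteria): the other MDP subscales, IC-RDOS and the respiratory parameters get the same unadjusted Student test, at 0.05.

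MDP-A1 is measured before and after the session in every patient (Table 1 and the description of the Multidimensional Dyspnea Profile).

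**The concern.** A change score uses baseline by subtracting it in full, which amounts to a fixed slope of 1. For a fluctuating symptom score the slope of post on pre is usually below 1. If the true slope is b and the arms differ by d in mean baseline, the expected difference in change is the treatment effect plus (b − 1)d. The arm that happens to start higher then looks more improved. A model that estimates b removes this linear component and has equal or smaller residual variance.

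This matters more in small arms, and there are only 21 patients in each. The Randomization section describes permuted blocks and mentions no stratification on baseline score. In addition, each two-group test estimates the variance from 42 patients although 63 are available. At stake is precision for the main comparison, in a trial planned with little power to spare.

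**Working it through.** **Inputs from the article:** difference 1, SD 1, alpha 0.025 per comparison, power 80%, 21 per arm, three arms allocated 1:1:1.

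**Assumptions:** two-sided tests (the article does not say); SD 1 is the SD of the differential, since that is the primary endpoint; pre-post correlation rho, not given, so a range is shown.

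**1. The plan's own figure.** The normal approximation gives n = 2(z₀.₉₈₇₅ + z₀.₈₀)² = 2(2.2414 + 0.8416)² = 19.01, so 20 per group. In the noncentral t calculation the noncentrality at n = 21 is 1/√(2/21) = 3.240 with 40 df and critical value 2.329, which gives power 0.815. At n = 20 power is 0.793. So 21 per group reproduces for exactly the planned test. A one-sided 0.025 would have given 17.

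**2. Size of a chance imbalance.** The SD of the difference between two arms' baseline means is √(2/21) = 0.309 baseline SDs. With equal pre and post variances and rho = 0.5, the slope is 0.5 and the change SD equals the single-score SD, here 1. An imbalance of one SD of that difference then shifts the change-score contrast by 0.5 × 0.309 = 0.15 points, against a planned effect of 1.

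**3. Variance under adjustment.** With equal pre and post variance s²:

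- change score: 2(1 − rho)s²
- baseline-adjusted residual: (1 − rho²)s²
- ratio: (1 + rho)/2

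**4. Power of the three-arm model at 21 per arm.** Residual df are 63 − 4 = 59, the critical value is 2.300, and the factor 1 + 1/58 allows for estimating the slope. Noncentrality = 1/√(ratio × (1 + 1/58) × 2/21).

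| rho | ratio | noncentrality | power | n per arm for 80% |
|---|---|---|---|---|
| 0.3 | 0.65 | 3.985 | 0.951 | 14 |
| 0.5 | 0.75 | 3.710 | 0.918 | 16 |
| 0.7 | 0.85 | 3.485 | 0.879 | 18 |
| 0.9 | 0.95 | 3.296 | 0.837 | 20 |
| 1.0 | 1.00 | 3.213 | 0.817 | 21 |

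The planned t-test stays at 0.815 throughout. Simulation with 8,000 runs per value gave 0.955, 0.915, 0.882 and 0.838 for rho 0.3, 0.5, 0.7 and 0.9. Pooling the variance over three arms without the covariate (60 df) gives 0.824, so about one point of each gain comes from pooling alone.

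**5. If the analysed baseline is cut off at 4.** Truncation shrinks the baseline variance by a factor k and leaves the slope and residual variance unchanged under a linear model. The ratio becomes (1 − rho²)/[(1 − rho²) + (1 − rho)²k], with rho the untruncated correlation. Assume an untruncated mean of 6 and SD of 2, so the cut lies one SD below the mean and k = 0.63. The change SD is again set to 1.

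- rho 0.3: 0.91/(0.91 + 0.49 × 0.63) = 0.75, power 0.92
- rho 0.5: 0.75/(0.75 + 0.25 × 0.63) = 0.83, power 0.89
- rho 0.7: 0.51/(0.51 + 0.09 × 0.63) = 0.90, power 0.86

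**6. If SD 1 meant the SD of a single score.** For rho 0.3, 0.5 and 0.7 the t-test would have power 0.659, 0.815 and 0.965, and the adjusted model 0.854, 0.918 and 0.985. The direction is the same.

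**The case against.** Endpoint, test and sample size agree with one another. Regression to the mean acts equally in expectation on randomized arms, so the t-test on change is unbiased and keeps its error rate. All of this stands, and it limits the point to efficiency.

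The gain rests on a correlation that the documents do not give. Both scores come from one session of about 1 h 30 min, so a high value is plausible. At 0.9 the gain is about 2 points, half of it from pooling. This also stands.

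Covariates are often left to an analysis plan, which is not shown, and the conclusions call the study a pilot. This carries less weight, because the article itself names the primary test.

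Four stronger readings are tempting, and the documents do not support them:

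- **That the plan ignores baseline.** It subtracts baseline to form the endpoint.
- **That selection at 4 or more increases the benefit of adjustment.** A cut-off reduces the baseline variance and hence the gain. The analysed pre-session score may also not be the entry score, because the inclusion visit section places the measurements after inclusion and randomization.
- **That adjustment removes imbalance at no cost.** It handles only linear imbalance in the measured baseline, spends one degree of freedom and assumes a common slope. Pooling also assumes a common variance.
- **That the t-test or the 21 per arm is wrong.** Neither is.

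**Conclusion.** The point holds as a recommendation to improve efficiency. The planned test is sound but gives up precision whenever the true slope of post on baseline differs from 1. With equal pre and post variances and a change SD of 1, power at 21 per arm rises from 0.815 to between 0.84 (correlation 0.9) and 0.95 (correlation 0.3). With a baseline cut off at 4, under the assumed mean of 6 and SD of 2, it is about 0.86 to 0.92 for untruncated correlations of 0.7 to 0.3. As the correlation approaches 1 the advantage almost vanishes (0.817), but in none of the cases computed does power fall below the plan. The exact gain cannot be fixed from the documents.

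**What to change.** Prespecify as the primary analysis one linear model of post-session MDP-A1 on arm (three levels) and baseline MDP-A1. With baseline in the model, using the differential as outcome gives the same arm contrasts. Test each active arm against placebo at 0.025 and report adjusted mean differences with confidence intervals. Keep the t-test on the differential as a sensitivity analysis, and use the same model form for MDP-QS, MDP-A2, IC-RDOS and the respiratory parameters.

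Centre may be added, since the trial has two centres, but this is optional: the Randomization section mentions no stratification by centre. With centre (58 df and a two-covariate allowance), power for correlations of 0.3, 0.5 and 0.7 would be about 0.948, 0.912 and 0.872.

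The cost is a change of wording, one degree of freedom and the assumptions of common slope and common variance. No extra measurement or patient is needed. The change must be fixed before unblinding, so that the choice to adjust cannot depend on the results.

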### Experimental Design

#### Randomization

After verification of the inclusion and exclusion criteria, the patients will be prospectively and randomly included in three groups of 21 patients, depending on the type of tDCS treatment received: anodal tDCS group, cathodal tDCS group, and placebo tDCS group. The tDCS will be applied up on the cortical representation zone of the primary motor and left pre-motor cortex for 30 min; intensity 2 mA (in anodal, cathodal, or placebo modality). The patient will be blinded from the randomization arm. Randomization will be performed on a dedicated and secure specific website (Cleanweb). Randomization will be carried out in a 1: 1: 1 ratio with permutation blocks of size unknown to the investigators.

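### The primary comparisons are set at 0.025, already halved for two tests, yet a Bonferroni correction is added "and applying Bonferroni correction if needed"-style without a rule, so it is not settled that 0.025 is final

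*Protocol article*

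**What the plan says.** Protocol article, Primary Judgment Criterion: the level is set by the words "Each experimental arm will be compared to the placebo group at risk 0.025". Student's t-test is named as the method, and the sentence closes with one more step: "and applying Bonferroni correction if needed". Just before this, the section lists anodal, cathodal and placebo as the conditions to be compared, but it gives a test level only for the two comparisons with placebo.

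Protocol article, Calculation Hypotheses for the Number of Subjects Required and Result: the alpha and its reason are given as "with a first species risk (alpha risk) of 2.5% (to take into account the 2 comparisons of each experimental group with placebo". Planned power is 80%. The target effect is stated per comparison: "Assuming a difference of 1 (on the primary efficacy endpoint, superiority study) between one of the 2 experimental groups and the placebo group". The assumed SD is 1. The result is 21 per group, 63 in total.

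Neither section says whether the tests are one-sided or two-sided.

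**The concern.** The two sections agree on the number 0.025, and the sample size section gives its origin: an overall 5% split over two comparisons. A Bonferroni correction has therefore already been made. The analysis section then provides for one as a further, conditional step. Both comparisons with placebo are always planned, so nothing in the design would make a correction needed in one case and not in another.

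At stake is how a primary p-value between 0.0125 and 0.025 would be read. With 0.025 as the final level it is a positive result; after a second halving it is a negative one. A stricter level would also no longer match the level at which the trial was sized.

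**Working it through.** **Inputs.** Difference 1, SD 1, alpha 0.025, power 80%, 21 per group (sample size section); equal allocation (Randomization section). Two-sided testing is an assumption, checked in step 1.

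**Method.** Two-sample t-test with n per group: df = 2n − 2; noncentrality = (difference/SD) × √(n/2); power = probability that a noncentral t variable falls beyond ± the critical value t(1 − α/2, df). For n = 21: df = 40 and noncentrality = √10.5 = 3.240.

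**Step 1: reproduce the plan's figure.**
- Two-sided 0.025: critical value 2.329, power 81.5%. With 20 per group power is 79.3%, so 21 is the smallest n that reaches 80%. The stated sample size is reproduced.
- Normal approximation: n = 2 × (2.2414 + 0.8416)² = 19.01, rounded up to 20.
- One-sided 0.025 would need only 17 (exact t) or 16 (normal). Two-sided 0.025 is therefore the reading that fits the document.

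**Step 2: power at 21 per group under the levels the clause could lead to (two-sided).**

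| Level per comparison | How it could arise | Exact t | Normal approx. |
|---|---|---|---|
| 0.025 | no further correction | 81.5% | 84.1% |
| 0.0167 | 0.05/3, all three pairs | 76.7% | 80.1% |
| 0.0125 | 0.025/2, second halving | 73.1% | 77.1% |
| 0.0083 | 0.025/3, three pairs on top of 0.025 | 67.8% | 72.7% |

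At 0.0125 the critical value is 2.616, and 80% power needs 24 per group (23 by the normal approximation). By the exact t-test, every further correction falls below 80%.

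**Step 3: how often the choice would matter.** Under the design assumptions, one comparison has p between 0.0125 and 0.025 with probability 81.5% − 73.1% = 8.4%. If both arms work as assumed, simulation puts the chance that at least one comparison falls there at about 16%.

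**Step 4: is a further correction needed for error control?** The two levels add up to 0.025 + 0.025 = 0.05, which bounds the family-wise error for the two comparisons with placebo. Simulation under no effect, with the shared placebo arm, gives about 4.6% at 0.025 each and about 2.4% at 0.0125 each. The second halving only gives away power.

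**Step 5: Holm for comparison.** The smaller p-value is tested at 0.025 and, if significant, the other at 0.05. If both arms differ from placebo by 1 with SD 1, the simulated chance of showing both is about 71% at 0.025 each, 80% with Holm and 60% at 0.0125 each. Family-wise error under Holm stays at 5% or less.

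**The case against.** The strongest reply is that the threshold is written down. "Each experimental arm will be compared to the placebo group at risk 0.025" is explicit, the sample size section gives the same number with its reason, and on the document's own terms no further correction for these two comparisons is needed. The clause may only name the method behind 0.025, or may be meant for an anodal-cathodal comparison. Much of this stands:

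- A reader might infer that the primary threshold is undefined. It is not: a nominal 0.025 appears in both sections. What is open is whether it is final.
- A reader might infer that the text prescribes 0.0125. It does not: the clause is conditional and gives no divisor, and 0.0125 is one reading among several.
- A reader might infer that the threshold is to be chosen after the data are seen. The article does not say when the need would be decided, so this is not shown.
- A reader might suspect an inflated false-positive rate. Every reading leaves the comparisons with placebo at 0.025 or stricter, so family-wise error stays at 5% or less.
- A reader might take plain Bonferroni to be a mistake. It is valid and matches the sample size, and the protocol sets no power target for showing both polarities. Holm is an option, not the correction of an error.

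What does not stand is that the benign readings settle the matter, because the text confirms neither. Nor is this a detail merely left to an analysis plan: the article itself states a level and then adds a correction without a rule.

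**Conclusion.** The point holds as a redundant clause without a rule in the primary analysis. The document gives 0.025 as the already adjusted level and then leaves room to adjust it again. Halving once more would lower power per comparison from 81.5% to 73.1%, about 8 percentage points, and below the planned 80%, with no need on grounds of error control.

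The figures rest on the protocol's difference of 1 and SD of 1, 21 analysed patients per group, an exact t-test and two-sided testing. If one-sided 0.025 were intended, halving it would still leave 81.5% power, but the stated calculation would then have given 17 per group and not 21. The size of the loss also depends on the reading and method: at 0.05/3 the normal approximation still gives 80.1%.

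Severity: should be fixed, not must be fixed. False-positive control is intact throughout, and the sample size agrees with 0.025.

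**What to change.** Delete the conditional Bonferroni clause from Primary Judgment Criterion. State instead that the two comparisons with placebo share a two-sided family-wise alpha of 5%, that 0.025 two-sided is the final level for each, and that no further correction applies. If an anodal-cathodal comparison on the primary endpoint is intended, say that it lies outside this family.

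As a free improvement, the same sentence can specify Holm: the smaller of the two p-values is tested at 0.025 and, if significant, the other at 0.05. This keeps family-wise error at 5% or less, leaves the sample size calculation at 2.5% valid and is never less powerful than 0.025 for each.

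Cost: one sentence in the protocol or analysis plan, made before unblinding. No extra patients and no loss of error control.
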